### Outcomes

The primary outcome is the proportion of correctly managed patients at 6 months. Secondary outcomes are the proportion of patients without symptoms at two and 6 months, and time to death. Other outcomes of interest are the proportions of patients with microbiologically-proven tuberculosis; with probable tuberculosis; with no tuberculosis; with a diagnosis other than tuberculosis; and receiving an invasive procedure. Safety outcomes are the occurrence of pneumothorax, major bleeding, and post-expansion pulmonary edema after interventions such as pleural tapping, ascites puncture or fine-needle aspiration.

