### Definitions

A patient is defined as having definite tuberculosis if any of the microbiological tests is positive (Xpert TB/RIF®, Xpert Ultra TB/RIF®, culture, acid fast bacilli in fine-needle aspiration from lymphnodes, adenosine deaminase (ADA) ≥ 40 U/ml in pleural fluid [21], ADA ≥ 35 U/ml in ascetic fluid [22], or ADA ≥ 35 U/ml in pericardial fluid [5].

A patient is defined as having probable tuberculosis if all microbiological tests are negative, and clinical, radiological and sonographic (in the intervention group) signs improve, and body weight is stable or increases after 2 months of anti-tuberculosis treatment. A patient is defined not to have tuberculosis if all microbiological tests were negative, and (a) clinical signs, symptoms and radiological signs (and in patients in the intervention group sonographic signs) improved, and body weight increased, without start of anti-tuberculosis treatment or (b) a diagnosis other than tuberculosis was found explaining the symptoms in a patient with or without anti-tuberculosis treatment.

A correctly managed patient is defined as one who had definite or probable tuberculosis and was treated with anti-tuberculosis treatment; or a patient who did not have tuberculosis and was not treated with anti-tuberculosis treatment.

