### Statistical analyses

Analyses and reporting will follow CONSORT guidelines (http://www.consort-statement.org/consort-2010) following intention to treat principles. Enrolment, randomisation and follow-up will be described using a flowchart. Baseline characteristics and outcomes will be described by group using frequencies and percentages for categorical variables and medians and interquartile ranges for continuous outcomes. The primary outcome will be compared between groups using logistic regression, reporting odds ratios with 95% confidence intervals. We will adjust for the stratification variables [23], and in sensitivity analyses for other baseline factors with imbalances between groups (by visual inspection, with no formal testing performed across groups) [24] or associated with missing primary outcome data [25]. We will assess effect modification of the primary outcome separately by HIV status and site, by using similar methods as for the primary outcome and an interaction between group and HIV status or site, respectively. Analyses of the categorical secondary and safety outcomes will follow similar methods as for the primary outcome, and with proportional hazards models for the time to death outcome if there are sufficient numbers of events. Inter-rater reliability of eFASH findings between the sonographer and the independent reviewer will be evaluated. A full statistical analysis plan will be developed.

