## Discussion

In 2018 an estimated 10 million new tuberculosis cases occurred worldwide, and 1.45 million people died of the disease [26]. Clinical symptoms can be sensitive, but not specific for tuberculosis [27]. Moreover, in HIV positive people on antiretroviral therapy, the absence of cough, fever, night sweats, or weight loss does not exclude tuberculosis, because of the low sensitivity of these symptoms in this group of patients [28]. Microbiological testing as the gold-standard remains challenging, with severely ill patients and patients with extrapulmonary tuberculosis who are often unable to expectorate sputum. Invasive sampling to acquire material for microbiology is mostly not available [29]. Furthermore, a strategy relying on spontaneously expectorated sputum is inadequate in about one third of tuberculosis cases [30]. Moreover, patients with tuberculosis and HIV often have low bacillary loads in sputum and other body cavity fluids, which reduces further the sensitivity of culture and Xpert MTB/RIF® assay [31]. Therefore, patients are often empirically treated despite negative microbiological tests [6]. Overtreatment of patients who do not have tuberculosis generates unnecessary costs, exposes patients to potentially toxic drugs, and might delay the diagnosis of the real cause of the disease. To our knowledge, this is the first randomized controlled trial to assess whether sonography, combined with chest X-ray and established microbiological tests, can increase the proportion of correctly managed patients with clinically suspected extrapulmonary tuberculosis.

This trial has some limitations: First, we cannot prevent doctors of patients in the control group from using sonography as part of routine care (not according eFASH protocol), which might reduce the real difference in outcomes between the groups. Second, the study is not blinded. However, results will reflect real life scenarios. Third, according to our experience in the observational study [9], loss to follow-up is a frequent challenge especially in the rural setting. We have attempted to address this through increasing our sample size to allow for some loss to follow-up. Fourth, this study is done in an environment with high tuberculosis prevalence, and findings cannot be transferred to low prevalence settings.

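### The definite, probable and no-tuberculosis classes behind the primary outcome are not exhaustive, and the protocol does not say how patients who fit none of them are scored

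*Protocol article*

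**What the plan says.** All references are to the protocol article. Under Outcomes: "The primary outcome is the proportion of correctly managed patients at 6 months". The Definitions section builds this on three classes.

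- **Definite tuberculosis:** "A patient is defined as having definite tuberculosis if any of the microbiological tests is positive". Adenosine deaminase thresholds count as positive tests.
- **Probable tuberculosis:** "A patient is defined as having probable tuberculosis if all microbiological tests are negative, and clinical, radiological and sonographic (in the intervention group) signs improve". A further condition concerns weight: "body weight is stable or increases after 2 months of anti-tuberculosis treatment".
- **No tuberculosis:** "A patient is defined not to have tuberculosis if all microbiological tests were negative, and (a) clinical signs, symptoms and radiological signs". Under (a) these signs, and sonographic signs in the intervention group, must have improved and weight must have risen with no anti-tuberculosis treatment started. Under (b) another diagnosis explains the symptoms, whether or not the patient was treated.

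The outcome follows from the class: "A correctly managed patient is defined as one who had definite or probable tuberculosis and was treated with anti-tuberculosis treatment". The other limb is a patient without tuberculosis who was left untreated. No residual class, default or adjudication rule follows.

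Under Outcomes, death appears only as a secondary endpoint (time to death). Statistical analyses commits to intention-to-treat principles. It plans sensitivity analyses adjusting for baseline factors that are imbalanced or "associated with missing primary outcome data", without saying which patients count as missing. Sample size allows 10% for loss to follow-up and nothing for patients who are followed but cannot be classified.

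**The concern.** Both routes to a class for a microbiology-negative patient without another diagnosis require improvement. Those who die or do not improve are therefore left without a class. Probable tuberculosis also presupposes treatment, so microbiology-negative tuberculosis that was never treated cannot be recorded at all.

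This matters for the comparison because the open gap sits on the post-randomisation course. The intervention algorithm changes who is treated, and improvement of sonographic signs is an extra condition in the intervention group only. The share of patients without a class may therefore differ between arms. If some analysts score them as failures and others set them to missing, the same data can give different answers, and the second choice conditions the analysis set on outcome.

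**Working it through.** **1. The plan's own figure.** Inputs from Sample size: 73% and 85%, two-sided alpha 0.05, power 95%. The pooled two-proportion formula gives 297 per arm, 594 in total, against 592 stated; power at 296 per arm is 95.0%. Inflation for 10% loss gives 592 × 1.10 = 651 or 592 / 0.90 = 658, against 650 stated. The sample size reproduces and is not in dispute.

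**2. Do the classes cover everyone?** For a microbiology-negative patient with no other diagnosis:

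| Treatment | Course | Class |
|---|---|---|
| Yes | Improved, weight up | Probable |
| Yes | Improved, weight stable | Probable |
| Yes | Not improved | None |
| Yes | Died before 2-month assessment | None |
| No | Improved, weight up | No TB (a) |
| No | Improved, weight stable | None |
| No | Not improved | None |
| No | Died before 2-month assessment | None |

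Five of these eight combinations have no class. With another diagnosis found, all eight fall under no TB (b), but the two that are treated and improved also meet probable TB. The first class makes them correctly managed and the second does not. Positive-microbiology patients are always definite TB.

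**3. If unclassified patients were excluded.** The share *u* without a class is not in the document; every value below is an assumption. Patients with follow-up: 650 × 0.90 = 585, or 292.5 per arm. Let 73% of all followed patients be correctly managed in both arms, so there is no true difference. The proportion among those kept is 0.73 / (1 − u).

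- u = 10%: 0.73 / 0.90 = 81.1%, n = 263.25
- u = 5%: 0.73 / 0.95 = 76.8%, n = 277.9
- Apparent difference: 4.3 points

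Rejection probability is Φ((|d| − 1.96 s₀) / s₁), with s₀ the pooled and s₁ the unpooled standard error: (0.0427 − 1.96 × 0.0351) / 0.0350 = −0.75, which gives about 23% against a nominal 5%. Exchanging the arms gives the same size with the opposite sign. With 15% against 10%, the figures are 85.9% and 81.1%, with about 30% rejection.

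**4. How far the scoring rule can move the result.** Assume now that 73% and 85% hold among classifiable patients (odds ratio 2.10 when the rest are excluded).

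- Unclassified 10% control, 15% intervention, scored as failures: 0.73 × 0.90 = 65.7% and 0.85 × 0.85 = 72.3%; odds ratio 1.36.
- Unclassified 15% control, 10% intervention: 0.73 × 0.85 = 62.1% and 0.85 × 0.90 = 76.5%; odds ratio 1.99.

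**5. Power with equal shares in both arms, same assumption.**

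| u | Excluded | Scored as failures | Difference if failures |
|---|---|---|---|
| 0% | 94.7% | 94.7% | 12.0 points |
| 5% | 93.7% | 89.2% | 11.4 points |
| 10% | 92.4% | 82.3% | 10.8 points |
| 20% | 89.3% | 67.4% | 9.6 points |

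**The case against.** The strongest reply is that nothing needs excluding. The article defines who is correctly managed, takes the proportion of patients who are, and commits to intention to treat; a patient who meets neither limb is simply not correctly managed. That is the natural literal reading, and it stands. A reader might infer that deaths and non-responders will vanish from the primary analysis and that the trial is not intention to treat. The documents do not support that: no sentence says such patients are dropped, and missing data are otherwise discussed only as loss to follow-up. What remains is that the text does not settle the choice.

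A reader might also infer that a larger sample ("We have attempted to address this through increasing our sample size to allow for some loss to follow-up") is the only answer offered to missing outcomes. It is not. Follow-up describes paid transport, phone calls and home tracing, and Statistical analyses has the adjusted sensitivity analysis. These address patients who are not seen, however, not patients who are seen and fit no class.

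A third tempting reading is that the gap favours the intervention. Empirical treatment in the control group could equally produce treated non-responders there, so the sign is unknown. Harm would also remain visible in time to death and symptom-free status, and deaths with a positive test or another diagnosis are still classified.

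Finally, a statistical analysis plan is announced and not shown, and it may hold a scoring rule. Methods for imputing true losses belong there and are not criticised here. The classes themselves, however, are set out in full in this article.

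**Conclusion.** The point holds as a defect in how the primary endpoint is fixed. Five kinds of microbiology-negative course have no class, two more meet two classes with opposite scores, and untreated microbiology-negative tuberculosis cannot be recorded. Whether unclassified patients are failures or missing is left open. That they will be excluded, or that the result will be biased in a given direction, is not established.

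The size cannot be read from the documents. On assumed exclusions of 10% and 5% with no true difference, the distortion is 4.3 points and rejection is about 23%, in favour of whichever arm loses more patients. With equal shares, exclusion costs little power. The classification gap rests on the text alone; every figure for its effect rests on assumed shares.

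**What to change.** Before outcomes are compared by arm, amend Definitions and Statistical analyses to state that:

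1. every patient with known vital status or a 6-month assessment who meets neither limb of correct management is scored as not correctly managed in the primary analysis;
2. only true loss to follow-up is a missing primary outcome;
3. the number of patients without a class is reported by arm, and a sensitivity analysis excludes them;
4. an untreated patient who improves with stable weight has a stated class;
5. one class takes precedence where probable tuberculosis and no tuberculosis (b) both apply.

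This needs wording and one added sensitivity analysis, with no new data and no change to patient care. Timing matters: the trial is open-label and 538 patients had been enrolled by the recruitment pause, so the rule should be dated and fixed without sight of outcomes by arm.

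The cost should be stated openly. Both proportions fall, and a treated death without another diagnosis counts as incorrect management, which mixes prognosis with diagnostic correctness; the sensitivity analysis is there to show how much that matters. If 73% and 85% were meant for classifiable patients only, power is about 82% at 10% unclassified and 67% at 20%, so the stated 95% should be read with that in mind.

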## Background

In resource-limited settings with a high tuberculosis prevalence, almost half of patients are treated empirically with anti-tuberculosis drugs upon clinical suspicion only [1–3]. Besides lack of available tests, this is mainly due to the poor sensitivity of microbiological tests, especially in patients co-infected with human immunodeficiency virus (HIV) or in those with suspected extrapulmonary tuberculosis [4, 5]. The decision to treat tuberculosis based on clinical signs and symptoms only has a low accuracy for culture-confirmed tuberculosis, and 30–60% of these decisions lead to false treatment [1, 3, 6]. The consequence is, that patients are unnecessarily exposed to potentially toxic drugs for long time periods, and the diagnosis of their real disease such as other infections, cancer or heart failure is delayed, or missed. Additional diagnostic methods are therefore needed to distinguish tuberculosis from other diseases with similar symptoms.

Ultrasound is a widely available diagnostic tool, which is used in various medical fields. Focused Assessment with Sonography for HIV and Tuberculosis (FASH) is a useful tool to detect signs of extrapulmonary tuberculosis, namely pleural and pericardial effusion, enlarged abdominal lymph nodes, hypoechogenic lesions in the spleen and the liver, ascites and thickening of the bowel wall [7]. FASH can be performed as a point of care bedside test and can be taught to personnel with little or no previous experience in ultrasonography [8]. In our observational study from rural Tanzania including 191 HIV-positive and -negative patients with suspected pulmonary or extrapulmonary tuberculosis, abnormal chest X-ray, presence of ≥1 FASH-sign, and elevated body temperature were independently associated with confirmed tuberculosis. A combination of ≥1 FASH sign, abnormal chest X-ray, and temperature ≥ 37.5 °C had a high (99.1%) sensitivity but a low (35.2%) specificity for confirmed tuberculosis. We concluded that ultrasound might be useful to exclude tuberculosis, in combination with other tests [9]. In a recent Cochrane metanalysis including HIV-positive adults, FASH signs predicted tuberculosis with a moderate diagnostic performance only. The authors also concluded that ultrasound results should be considered in combination with other tests, such as chest X-ray and Xpert MTB/RIF® only [10]. No randomized controlled trial evaluating sonography for the diagnosis of tuberculosis has been done yet.

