### Randomization

The randomization list was prepared in advance by the statistician, stratified by site (Ifakara and Mwananyamala) and HIV status (positive or negative) with randomly-varying block sizes. Patient allocation was done in a 1:1 ratio to the intervention or control group.

The sequence was concealed by using envelopes prepared by an independent person, based on the list prepared by the statistician. The envelopes are opaque and sealed, labelled only with the stratification information and a sequential number. Inside the envelope is a piece of paper confirming the stratification information and sequential number, and indicating the group allocation. The envelopes are stored securely. Checks are performed intermittently during enrolment to ensure that the randomization sequence is being respected.

Allocation of patients to the intervention or control group is done by the study clinical officers at each study site, after history taking, physical examination, collection of blood, urine and sputum for laboratory and microbiological examinations, chest X-ray, HIV testing, and informed consent. Based on the stratification of the patients (i.e site and HIV status), the study clinical officers take the next sequentially numbered envelope. They verify the information inside the envelope, and store the allocation paper in the patient file for source document verification if necessary.

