### Sample size

Assumptions for the sample size calculation were based on data from the literature [1, 3, 6] and preliminary analysis of our observational study [9] (Table S2). Based on these assumptions, 73 and 85% of patients in the control and intervention groups, respectively, would be correctly managed. For a power of 95% with a two-sided alpha of 0.05, this yields a sample size of 592 patients. Assuming a lost to follow-up of 10%, 650 patients are required.

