In conclusion, this study is the first randomized controlled trial investigating ultrasound in the management of extrapulmonary tuberculosis. We hypothesize that ultrasound, added to other tests, will increase the proportion of correctly-managed patients, and therefore reduce overtreatment with anti-tuberculosis drugs.

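### Probable tuberculosis is defined by recovery on treatment, so the primary outcome undercounts overtreatment by an unknown amount and cannot by itself support an overtreatment conclusion

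*Protocol article*

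**What the plan says.** The primary outcome is the proportion correctly managed at 6 months. Under Definitions, "A correctly managed patient is defined as one who had definite or probable tuberculosis and was treated with anti-tuberculosis treatment"; the other way to be correct is not to have tuberculosis and not to be treated for it.

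The same section sets the categories:

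- *Definite tuberculosis*: any positive microbiological test, including the adenosine deaminase thresholds.
- *Probable tuberculosis*: all microbiology negative, signs improved (sonographic signs too, in the intervention group), and weight stable or up after 2 months on treatment.
- *No tuberculosis*: all microbiology negative and either (a) signs improved and weight increased with no treatment started, or (b) another diagnosis explains the symptoms, whether or not the patient was treated.

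The Background motivates the trial by overtreatment: for decisions made on clinical signs alone, judged against culture, "30–60% of these decisions lead to false treatment". The closing paragraph of the Discussion hypothesises that ultrasound "will increase the proportion of correctly-managed patients, and therefore reduce overtreatment with anti-tuberculosis drugs", and the Abstract draws the same link. Under Outcomes, the further outcomes begin: "Other outcomes of interest are the proportions of patients with microbiologically-proven tuberculosis; with probable tuberculosis; with no tuberculosis". Other diagnosis and invasive procedures follow. Neither the proportion treated nor the proportion treated without tuberculosis is listed. The limitations in the Discussion do not mention the dependence of disease status on treatment.

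**The concern.** The reference standard contains the decision it is meant to judge. Take one patient with negative microbiology and a condition that would resolve anyway. If treated, the patient becomes probable tuberculosis and is correct. If left untreated, and provided weight rises, the patient becomes no tuberculosis and is also correct. The outcome cannot tell these two decisions apart, although telling them apart is the stated reason for the trial.

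Three things are at stake. The treatment contrast may be distorted. The distortion may differ between arms in an open-label trial. And a higher proportion correctly managed may be reported as less overtreatment when the outcome does not measure that.

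**Working it through.** **1. How each treated, microbiology-negative patient is scored under Definitions**

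| Course on treatment | Other diagnosis found | Category | Scored correct? |
|---|---|---|---|
| Improves, weight stable or up | No | Probable | Yes |
| Improves, weight stable or up | Yes | Meets both probable and no tuberculosis (b) | Not determined: no precedence rule |
| Does not meet the improvement criteria | Yes | No tuberculosis (b) | No |
| Does not meet the improvement criteria | No | None of the three | No |

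The undercount is therefore confined to treated patients who recover. The first row is always affected, and the second is affected if probable takes precedence.

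**2. The planned figure**

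The Sample size section plans on 73% correct in control and 85% in intervention, and its result is "For a power of 95% with a two-sided alpha of 0.05, this yields a sample size of 592 patients". The total is then raised to 650 to allow for 10% loss, and Randomization gives 1:1 allocation. The two-proportion formula without continuity correction gives 594 with pooled variance and 586 with unpooled. Power at 296 per arm is 95.0%. The stated 592 is reproduced, so the arithmetic is sound.

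**3. Illustration, equal re-scoring in both arms**

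The document does not give two of the inputs, which are assumed:

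- s = share of planned errors (27% control, 15% intervention) that are overtreatment;
- r = share of those overtreated patients who are scored as probable tuberculosis.

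It is also assumed that 73% and 85% are rates against the truth, before any re-scoring. Then:

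- control = 0.73 + 0.27·s·r
- intervention = 0.85 + 0.15·s·r
- difference = 0.12·(1 − s·r)

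For s = 0.8 and r = 0.5: control 0.73 + 0.27 × 0.40 = 0.838; intervention 0.85 + 0.15 × 0.40 = 0.910; difference 0.072.

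| s | r | Control | Intervention | Difference (points) | Power at 592 |
|---|---|---|---|---|---|
| 0.5 | 0.5 | 79.8% | 88.8% | 9.0 | 85% |
| 0.8 | 0.5 | 83.8% | 91.0% | 7.2 | 75% |
| 0.8 | 0.7 | 88.1% | 93.4% | 5.3 | 60% |
| 0.8 | 0.9 | 92.4% | 95.8% | 3.4 | 41% |

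Over s from 0.6 to 1.0 and r from 0.3 to 0.9, power runs from 89% down to 17%.

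**4. Illustration, unequal re-scoring (s = 0.8)**

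The arms have reasons to differ. Sonographic improvement is required only in the intervention group, that group's algorithm prompts a search for other causes, and assessment is unblinded.

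| r control | r intervention | Control | Intervention | Difference (points) | Power at 592 |
|---|---|---|---|---|---|
| 0.5 | 0.3 | 83.8% | 88.6% | 4.8 | 39% |
| 0.5 | 0.7 | 83.8% | 93.4% | 9.6 | 96% |
| 0.3 | 0.6 | 79.5% | 92.2% | 12.7 | 99% |

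The difference can fall well below 12 points or exceed it. With s = 1, r of 0.5 in control and 0.1 in intervention removes it altogether (86.5% in both arms).

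**5. The composite does not identify overtreatment**

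Even with perfect classification, 27% and 15% are totals of two error types. If half the control errors were overtreatment (0.5 × 27% = 13.5%) and all the intervention errors were (15%), correct management would rise from 73% to 85% while overtreatment rose from 13.5% to 15%. This split is hypothetical. It shows only that the inference from one to the other does not follow.

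**The case against.** **Some overtreatment is still counted.** A reader might infer that the trial cannot show any reduction in overtreatment, or that unnecessary treatment counts as an error only when another diagnosis turns up. The definitions do not support either reading. Treated, microbiology-negative patients who fail the improvement or weight criteria are not scored correct, with or without another diagnosis, and route (b) expressly covers treated patients. This stands: the outcome undercounts overtreatment but is not blind to it.

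**The trial may not be underpowered.** The 73% and 85% come from literature and a preliminary analysis of the team's observational study, detailed in Table S2, which is not shown. If those rates already used the trial's definitions, the illustration in step 3 counts the effect twice and power stays at 95%. Unequal re-scoring can also raise power. This stands too: the figures show sensitivity, and a firm claim of lost power or of a known direction of bias is not supported.

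**Overtreatment is an aim, and detail belongs in the analysis plan.** The Discussion states a hypothesis and the Abstract states what the study will determine; neither reports a result. A statistical analysis plan is promised, and crossing the listed categories with treatment status would give the proportion treated without tuberculosis. This lowers the severity. It does not remove the point, because the outcome definition and the inference from it to overtreatment are both fixed in this document, and the listed categories carry the same circularity.

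**Treatment without positive microbiology is not overtreatment.** The intervention algorithm deliberately treats some microbiology-negative patients, and the article stresses how insensitive microbiology is in extrapulmonary disease. This stands, so that proportion can only be descriptive.

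**Conclusion.** The concern holds in a limited form. The treatment decision is built into the reference standard. Overtreatment is missed among treated patients who recover unless another diagnosis is found, and even then the missing precedence rule leaves the score open. The size of the undercount is unknown, and so is the direction of its effect on the group difference, because re-scoring may differ by arm.

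Equal re-scoring would shrink the 12-point difference by the factor (1 − s·r), for example to 7.2 points and about 75% power at s = 0.8 and r = 0.5. This rests on assumed s and r, on equal r in both arms, and on 73% and 85% being free of re-scoring; none of these can be checked here.

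Independently of those assumptions, a rise in correct management does not by itself show less overtreatment. No listed outcome closes that gap, and the limitations do not disclose it.

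**What to change.** Keep the primary outcome. Before analysis, pre-specify:

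- **(a) Precedence.** A rule stating which category applies when a treated, microbiology-negative patient both improves and has another diagnosis.
- **(b) Sensitivity analyses by arm.** Re-score treated, microbiology-negative responders as not having tuberculosis, using the same evidence in both arms (so not requiring sonographic improvement in one arm only). Full re-scoring is an extreme bound and should be labelled as such.
- **(c) Error types.** Split incorrect management by arm into treated without tuberculosis and tuberculosis not treated.
- **(d) Treatment starts.** Report the proportion started on anti-tuberculosis treatment, overall and without positive microbiology, on all randomised patients. This is a descriptive comparison that does not itself measure overtreatment, so no conclusion should be made conditional on it.

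State the incorporation bias as a limitation. Draw a conclusion about overtreatment only if the proportion treated without tuberculosis in (c) is lower in the intervention arm and this holds up in (b).

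The cost is analysis-plan wording, a few extra tables and a more cautious conclusion. Treatment and test results are already needed for the primary outcome, and no treatment rule changes. The Timeline section reports 538 patients included of the 650 planned, with recruitment paused, so at the time of the article this could still be fixed before analysis.
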